### 2.14. Exploratory outcome indicators

The exploratory outcome is the level of IL-1β, IL-2, MCP-1, cartilage oligomeric matrix protein (COMP), and tumor necrosis factor TNF-α in serum. Interleukin-1β is a key virulence factor for osteoarthritis.^[35]^ As a pro-inflammatory factor released by helper T cells, IL-2 stimulates the activation of relevant effector cells, resulting in the damage of synovium and cartilage in the joint.^[36]^ Studies have shown that higher levels of COMP are associated with higher severity of KOA, and vice versa indicating a lower degree of KOA.^[37,38]^ Increased levels of MCP-1 promote the conversion of monocytes into macrophages in the joint capsule,^[39]^ promote the development of an inflammatory response, and cause inflammatory damage to the joint capsule. The 5 mL fasting venous blood will be obtained before treatment and 4 weeks after treatment. After standing, the serum will be centrifuged, and the tubes will be placed in a refrigerator at 80°C for testing. The changes in the above markers in serum will be detected by enzyme-linked immunosorbent assay and Human Cytokine Array Kit. In order to reduce the influence of the circadian rhythm, each blood draw will take place between 10 and 11:30 in the morning. We will use the human cytokine array kit from R&D Systems to analyze osteoarthritis-associated cytokines in subjects’ serum. In addition to detecting the IL-1β, IL-2, MCP-1, and COMP, the kit can also detect additional 28 cytokines, so we can also explore whether other factors are involved in the pathogenesis of osteoarthritis.

### 2.15. Data collection and management

All of our measures are free of charge in order to ensure that subjects are fully followed. The case report form will be completed on paper and then entered into the spreadsheet. The School of Acupuncture and Massage, Shanghai University of Traditional Chinese Medicine will keep the original case report form and other forms (including informed consent forms). The required data will be collected according to the following case data collection schedule (Table 1). The Research Ethics Committee of Shanghai Municipal Hospital of Traditional Chinese Medicine will be independent of the investigators and the sponsor to audit the trial implementation every 6 months and decide whether to terminate the study early.

**Table 1 T1:** Case data collection timetable.

	Before treatment	Week 2	Week 4	Week 8	Week 12	Week 24
Signing informed consent	√	—	—	—	—	—
Concomitant treatment	√	—	—	—	—	—
History of medication	√	—	—	—	—	—
Bilateral standing knee joint radiography	√	—	—	—	—	—
WOMAC	√	√	√	√	√	√
VAS	√	√	√	√	√	√
SF-36	√	—	√	—	√	√
Subject self-evaluation	—	—	√	—	√	—
Subject feeling during treatment (collected at each treatment)	√	√	√	—	—	—
Serum marker	√	—	√	—	—	—
Safety evaluation (collected each time you visit and follow up)	—	√	√	√	√	√
Other:						
Chinese medicine intake	√	√	√	√	√	√
Daily drug record (collected each time you visit and follow up)	√	√	√	√	√	√

SF-36 = short-form health survey; VAS = visual analog scale, WOMAC = Western Ontario and McMaster Universities Osteoarthritis Index.

### 2.16. Sample size

In the previous study of the study group, the mean value of pain improvement of WOMAC in patients with KOA in the traditional moxibustion group was 184.87. The 10% of the mean difference in pain improvement in the moxibustion group was used as the non-inferiority margin δ,^[40]^ that is, δ = 18.49, which was jointly determined by a statistician and a clinical expert engaged in KOA research. We used the non-inferiority test to calculate the sample size, α = 0.025, 1-β = 80%, which was calculated by the sample size estimation software PASS20.0.1 (PowerAnalyand SampleSize, PASS20NCSS), resulting in that 38 subjects were required in each group (see Fig. 1). In order to prevent dropouts leading to an inadequate sample size, a dropout rate of 15% was preset, and we would recruit 44 subjects per group, which required a total of 88 subjects to be recruited.

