## 2. Method

### 2.1. Study design

This is a non-inferiority randomized single-blind controlled clinical trial, which aims to compare the treatment of typical inflammatory pain (KOA) with herbal activated carbon smokeless moxibustion and traditional moxibustion. The protocol has been registered in the Chinese Clinical Trial Registry (No. ChiCTR2200057923) and will be implemented in accordance with the declaration of Helsinki. Eligible participants will be randomly divided into 2 groups (new smokeless moxibustion group or traditional moxibustion group), with a distribution ratio of 1:1. The whole study will include 4 weeks of treatment and an additional 20 weeks of follow-up. The patient will be informed: You will have a 1 in 2 possibilities of receiving smokeless moxibustion or traditional moxibustion. Prior to randomization, written consent should be obtained from each participant.

An overview of the study process is shown in Figure 1.

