### 2.3. Inclusion criteria

Age 40 to 75 years.According to the diagnostic criteria of KOA of the American rheumatology society.^[21–25]^Radiographic confirmation of KOA (Kallgren Lawrence grade ≥ 1).^[26–28]^Moderate or more severe knee pain for most of the past month; the subject’s visual analog scale baseline score for arthritic pain is 40 points and above.Agree to accept the random assignment, understand, and be willing to sign the informed consent form.

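### The 80% power for 38 per group rests on an unstated SD and an unstated true difference; at zero difference it needs an SD of about 28 to 29, for which the document offers no support

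*Protocol article*

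**What the plan says.** All the figures are in section 2.16 of the protocol article.

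- Reference improvement, from the group's own previous study: "the mean value of pain improvement of WOMAC in patients with KOA in the traditional moxibustion group was 184.87".
- Margin, set at 10% of that mean: "that is, δ = 18.49, which was jointly determined by a statistician and a clinical expert".
- Error rates: "We used the non-inferiority test to calculate the sample size, α = 0.025, 1-β = 80" (per cent). Whether alpha is one-sided or two-sided is not said.
- Result: "resulting in that 38 subjects were required in each group".
- Dropout: "a dropout rate of 15% was preset, and we would recruit 44 subjects per group", "which required a total of 88 subjects to be recruited".

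Section 2.1 gives the allocation ("with a distribution ratio of 1:1"). Section 2.12 makes change in WOMAC pain from baseline to week 24 the primary outcome, and section 2.17 compares the groups with a t test.

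No section gives an SD for the change, an assumed true difference between the products, or the range of the WOMAC pain scale in use.

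**The concern.** For a comparison of two means, the sample size depends on the ratio of the margin to the SD. Section 2.16 names the software and gives the margin, alpha, power and answer, but omits the SD. The answer therefore has to be read backwards, and it then implies that patients' improvements cluster tightly around the mean.

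The outcome is self-reported pain 24 weeks after baseline, 20 weeks after treatment ends. It is returned by post (section 2.13), in patients who may keep taking their analgesics (sections 2.7 and 2.13). A tight spread cannot be taken for granted in that setting.

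The trial's main conclusion is at stake. If the true SD is well above the implied one, two equally effective products would often fail to show non-inferiority, and the stated 80% would have misled readers about that risk.

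The allowance for dropout also looks slightly too small.

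**Working it through.** **Inputs (section 2.16 unless noted).** Mean improvement 184.87; margin δ = 18.49; alpha 0.025, read as one-sided because the test is for non-inferiority; power 80%; n = 38 per group; dropout 15%; 44 per group; allocation 1:1 (section 2.1). True difference taken as 0, which is an assumption.

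**1. The margin.** 0.10 × 184.87 = 18.487, which agrees with 18.49.

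**2. The 38.** The formula is n = 2(z₁₋α + z₁₋β)² SD²/δ². Without an SD it cannot be run forwards. Solved for the SD:

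- Normal approximation: SD = δ√(n/2)/(z₁₋α + z₁₋β) = 18.49 × √19/2.8016 = 28.77, which is 15.6% of 184.87.
- Noncentral t with 74 degrees of freedom: SD = 28.39, which is 15.4% of 184.87.

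If improvements were roughly normal with SD 28.39, about 95% of patients would improve by 184.87 ± 1.96 × 28.39, that is, by 129 to 241 points.

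**3. Sensitivity of the implied SD to the other unstated inputs.**

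- One-sided alpha 0.0125: SD 25.7 to 26.1. One-sided alpha 0.05: SD 32.1 to 32.4.
- True advantage of the new product of 5 points: 28.39 × 23.49/18.49 = 36.1 (normal approximation 36.5).
- True advantage of 10 points: 28.39 × 28.49/18.49 = 43.7 (normal approximation 44.3).

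**4. Power of 38 per group at larger SDs.** The SDs after the first row are illustrative assumptions; the document gives none. Power and required n use the noncentral t at zero true difference. The 95% CI half-width is 1.9925 × SD × √(2/38) = 0.4571 × SD.

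| SD of change | SD as % of 184.87 | Power, 38 per group | n per group for 80% | CI half-width |
|---|---|---|---|---|
| 28.39 | 15% | 80% | 38 | 13.0 |
| 35 | 19% | 62% | 58 | 16.0 |
| 40 | 22% | 51% | 75 | 18.3 |
| 50 | 27% | 36% | 116 | 22.9 |
| 60 | 32% | 26% | 167 | 27.4 |
| 75 | 41% | 18% | 260 | 34.3 |

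The half-width equals the margin at SD = 18.49/0.4571 = 40.4. Above that, an observed difference of exactly zero would not establish non-inferiority.

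**5. Dropout.** 38/(1 − 0.15) = 44.7, so 45 per group (90 in total). The stated 44 is what 38 × 1.15 = 43.7 gives when rounded up. With 44 recruited, 44 × 0.85 = 37.4 remain, below 38. At SD 28.77 (normal approximation) power is 79.4% with 37.4 per group against 80.0% with 38. The dropout that 44 can absorb is 1 − 38/44 = 13.6%.

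**The case against.** The strongest reply is that an omitted input is not a wrong one. The article condenses a longer protocol, the previous study may have supplied an SD near 28, and a modest assumed advantage for the new product would admit a larger SD. This stands to the extent that 38 cannot be called an error. It does not remove the point. Section 2.16 chose to present the calculation, and the two inputs left out decide whether the 80% is credible. If an advantage was assumed, that assumption is driving the sample size and needs to be visible.

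A reader might go further and infer that the entry criterion, "visual analog scale baseline score for arthritic pain is 40 points and above", contradicts so small an SD, because entry pain can vary widely. The documents do not support that. The criterion (section 2.3) is a baseline threshold on a visual analog scale, while the disputed quantity is the SD of change in WOMAC pain. No WOMAC range or entry limit is given. A spread in baseline scores does not fix the spread of change: if patients improved by similar absolute amounts, baseline variation would add nothing. Getting from one to the other takes a mapping between instruments, a response model and an assumed baseline distribution, none of which the plan contains.

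On dropout, it is fair to say that one patient per group is close to rounding and costs less than one percentage point of power.

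**Conclusion.** The point holds as an undisclosed and unsupported assumption, with a small arithmetic slip beside it. At zero true difference and one-sided alpha 0.025, the stated power requires an SD of about 28 to 29, some 15% of the mean improvement. The back-calculation is firm given those two readings. The power figures at larger SDs depend on assumed SDs and show how sensitive the design is; they do not predict what will happen.

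It would be too strong to conclude that 80% power is unattainable at any realistic spread, or that an inconclusive result is likely. The documents contain no SD, and the previous study's data are not available, so an SD of 28 may be optimistic but has not been shown to be wrong.

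The dropout slip is shown by the plan's own figures and is minor: one patient per group, power 79.4% in place of 80.0%.

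**What to change.** In section 2.16:

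1. State the SD of WOMAC pain change and its source, confirming that it comes from the same form of WOMAC and the same time point as the primary outcome. State the assumed true difference and that alpha is one-sided, if it is.
2. Restate the power of 38 evaluable patients per group at that SD, with a short table over larger SDs. If the power is below 80%, replace the 80% figure.
3. Correct the dropout statement. Either keep 88 and say that it covers 13.6% dropout, or give 45 per group (90 in total).

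The cost is wording, and possibly a less favourable stated power. No extra patients are needed if 88 is kept; the alternative adds two.

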### 2.17. Statistical analysis

The intent-to-treat analysis is the principle of this study and includes all subjects in a given treatment arm as well as subjects who complete at least 1 treatment course. The level of significant difference is set at 0.05. Baseline characteristics will be summarized for both groups of subjects. For continuous results, the normal distribution of the data is labeled as the mean (standard deviation). The primary outcome measure is the effect value of the WOMAC pain score from baseline, using the *t* test to compare the smoke-free moxibustion group with the traditional moxibustion group. For secondary outcomes, unpaired scores including WOMAC Pain, Function, and Stiffness Scores, Short-Form health survey 36, Expectedness and Reliability of Treatment, and Overall Treatment Outcomes will be compared at all follow-up time points in both groups. Continuous variables will be compared using *t* test or Wilcoxon rank-sum test. We will use SPSS version 22 (IBM SPSS Statistics, New York, NY) for statistical analysis.

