Effective intervention on KOA may reduce knee pain, prevent complications, and even help to reduce mortality.^[15]^ Traditional moxibustion is a widely used characteristic treatment technology of traditional Chinese medicine, which is often used to treat KOA.^[16–18]^ However traditional moxibustion has some defects like time-consuming and laborious, the flame is easy to cause ambustion, and the treatment room also has many requirements. In particular, the smoke generated in the combustion process is not conducive to the health of physicians and patients which to a certain extent restricts its clinical application. The mechanism of moxibustion is related to its warm effect and radiation effect. The previous study of our research group found that the combustion temperature of plant herbal activated carbon smokeless moxibustion is close to that of traditional moxibustion. Infrared radiation characteristics peak of two kinds of moxibustion are similar to that of human acupoints deducting blackbody radiation and adenosine triphosphate energy metabolism, and can resonate with the molecules in acupoints and body tissues to produce curative effect, providing the physiological physics basis that smokeless moxibustion can be used as an alternative material for traditional moxibustion. It has been reported that infrared radiation has effects on cellular adenosine triphosphate metabolism, cyclooxygenase concentration, and bone repair.^[19,20]^ The efficacy of herbal active carbon smokeless moxibustion in the treatment of KOA has not been evaluated in clinical trials. The hypothesis is that 3 sessions per week of 2 kinds of moxibustion will have the clinical effect on KOA.

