## 3. Discussion

The purpose of this study is to explore smokeless moxibustion as an effective moxibustion supplement and alternative therapy for the treatment of KOA. The trial will assess its non-inferiority compared to traditional moxibustion. Participants will receive 3 treatments per week. For external treatment of traditional Chinese medicine, the frequency of 3 times a week is the most commonly used method for the treatment of KOA. The use of single-blind randomized controlled trials in this trial can ensure the safety of subjects during the trial, and can also avoid the positive or negative effects of bias caused by subjective preferences for different therapies. This trial is a multicenter trial, which facilitates the collection of cases in a wide range in a short period of time, and the results are also more representative. This trial has some limitations. Due to the differences in the moxibustion materials used for smokeless moxibustion and traditional moxibustion, the operator will understand the grouping before placing the moxibustion box, which may lead to the operator’s basis. Therefore, operators will be rigorously trained in the assessment, treatment, follow-up, etc prior to the study. Traditional moxibustion produces strong smoke, which can be harmful to health,^[41]^ so many clinics and hospitals do not perform moxibustion therapy. New smoke-free moxibustion solves the problem of smoke produced by traditional moxibustion and also retains the warm effect, infrared characteristics, and unique odor of traditional moxibustion. Exploratory studies will help to determine the effect of new smokeless moxibustion and traditional moxibustion on serum parameters of KOA and explore objective parameters of clinical efficacy of KOA. This trial will provide reliable evidence for new smokeless moxibustion in the treatment of KOA and compensate for the lack of clinical efficacy research in this field.

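### The trial is declared and sized as non-inferiority, but the stated primary analysis is a t test for a difference, with no margin and no rule for concluding non-inferiority

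*Protocol article*

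**What the plan says.** Three sections of the protocol article set a non-inferiority question.

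- Section 2.1: "This is a non-inferiority randomized single-blind controlled clinical trial".
- Section 2.16: "We used the non-inferiority test to calculate the sample size, α = 0.025, 1-β = 80" per cent. The margin is 10% of the traditional group's earlier mean improvement: "the mean value of pain improvement of WOMAC in patients with KOA in the traditional moxibustion group was 184.87", and "that is, δ = 18.49, which was jointly determined by a statistician and a clinical expert". The result is stated as "resulting in that 38 subjects were required in each group", raised to 44 per group for 15% dropout.
- Section 3: "The trial will assess its non-inferiority compared to traditional moxibustion".

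Section 2.17 fixes the primary analysis. It sets the general level with "The level of significant difference is set at 0.05" and says that the change in WOMAC pain will be compared between the two arms by t test. It names no margin, no confidence interval, no one-sided level and no criterion for declaring non-inferiority.

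**The concern.** The sample size was computed for one hypothesis and the analysis is described for another. Section 2.16 plans to rule out that smokeless moxibustion is worse by 18.49 or more. Section 2.17, read at face value, asks whether the arms differ at all.

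If smokeless moxibustion is about as good as the traditional form, the expected result of that test is a non-significant one, which does not show that the deficit is smaller than the margin. Only a significant result in favour of smokeless moxibustion would carry non-inferiority with it, and the trial was not designed around that outcome.

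The trial's main conclusion is therefore left without a stated decision rule. A reader or analyst who follows section 2.17 could take p > 0.05 as the hoped-for finding.

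**Working it through.** **Inputs.** From section 2.16: earlier mean improvement 184.87, margin δ = 18.49, alpha 0.025 (sidedness not written; read as one-sided, as is usual for a non-inferiority test), power 80%, n = 38 per group. From section 2.17: t test, level 0.05 (read as two-sided). The SD is not stated.

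**Step 1. Margin.** 0.10 × 184.87 = 18.487, which rounds to the stated 18.49.

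**Step 2. Sample size, solved backwards.** With a true difference of 0, n = 2·SD²·(1.960 + 0.842)² / δ². Because the SD is missing, n = 38 cannot be reproduced, only inverted: SD = 18.49 × √(38/2) / (1.960 + 0.842) ≈ 28.77 at the upper end. Allowing for rounding up to 38, the SD lies between about 28.4 and 28.8 by the normal formula, or 28.0 and 28.4 by the t-based version. I use 28.4, where the two ranges meet.

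**Step 3. Which analysis the sample size assumes.** At SD 28.5, a one-sided alpha of 0.05 would need only 30 per group. At an SD near 28.4, n = 38 therefore fits a margin-based test at one-sided 0.025, equivalent to a two-sided 95% confidence interval set against −18.49.

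**Step 4. How often p > 0.05 occurs when the true deficit equals the margin.** The standard error is SD × √(2/38), with 74 degrees of freedom and critical value 1.9925. At SD 28.4 the standard error is 28.4 × √(2/38) = 6.515 and the non-centrality is 18.49 / 6.515 = 2.838. The non-central t distribution then gives:

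| SD | Status of SD | P(two-sided p > 0.05), true deficit 18.49 | Margin-based test concludes non-inferiority |
|---|---|---|---|
| 28.4 | back-solved from n = 38 | 20.0% | 2.5% |
| 40 | assumption | 48.8% | 2.5% |
| 50 | assumption | 64.4% | 2.5% |

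The 20% at SD 28.4 is the complement of the 80% power: a trial sized to exclude a deficit of 18.49 also has about 80% power to detect one. If all 44 per arm were evaluable, the figure at SD 28.4 would be 14.5%.

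**Step 5. Where the two readings disagree on the same data.** At SD 28.4 the 95% half-width is 1.9925 × 6.515 = 13.0.

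- The difference is not significant if the observed deficit is below 13.0.
- Non-inferiority is shown only if the observed deficit is below 18.49 − 13.0 = 5.5.
- An observed deficit between about 5.5 and 13.0 is therefore not significant, yet fails the margin.

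**The case against.** The strongest defence is that the pieces are all present. The margin and alpha stand in section 2.16. A t test is the usual vehicle for non-inferiority on means, being the same statistic shifted by the margin. Section 2.17 does not write out a null hypothesis, so one could read it as naming the test and section 2.16 as supplying the margin, with the formal rule left to a fuller document. This reading is possible, but the article does not support it: the only level given in section 2.17 is worded as a level for a difference, and nothing there points back to the margin. The article commits to a specific test and level, and those belong to a different question.

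Other parts of the defence stand and limit the point.

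- A reader might infer that the investigators will treat a non-significant result as non-inferiority. No section says how such a result will be interpreted. The 20% is the error rate of a possible misreading, not of a stated rule.
- A reader might infer that p > 0.05 is the likely result even at a full-margin deficit. At the only SD that the article's figures imply, it occurs in about one trial in five. It passes one half only at an assumed SD a little above 40.
- A reader might see 0.05 against 0.025 as a contradiction. Used as a two-sided 95% confidence interval against the margin, 0.05 is the same as one-sided 0.025.
- The Introduction's sentence, "The hypothesis is that 3 sessions per week of 2 kinds of moxibustion will have the clinical effect on KOA", is not a non-inferiority hypothesis, but it is loosely worded background and the point does not depend on it.

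**Conclusion.** The point holds in this form: section 2.17, followed as written, does not test the question that sections 2.1, 2.16 and 3 set. The fault is the absent margin and hypothesis in the primary analysis, not the level of 0.05.

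If a non-significant t test were taken as non-inferiority, the false-claim rate at a true deficit of 18.49 would be about 20% rather than 2.5%, roughly eight times the design level. That figure rests on 38 evaluable per arm, a two-sided test, and an SD of about 28.4, itself back-solved assuming one-sided 0.025, 80% power and no true difference. The higher rates at SD 40 and 50 only illustrate the direction if the SD is larger; the article gives no support for those values. The conflict between the sections does not depend on any SD.

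It should be settled before data are seen, because the two readings can give opposite answers on the same results.

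**What to change.** In section 2.17, and in any analysis plan that follows from it, state:

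- H0: difference in mean WOMAC pain improvement from baseline to week 24 (smokeless minus traditional) ≤ −18.49; H1: difference > −18.49.
- Non-inferiority is concluded only if the lower limit of the two-sided 95% confidence interval for that difference (one-sided alpha 0.025) exceeds −18.49.
- A non-significant test of difference is not evidence of non-inferiority.

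The SD behind n = 38 should be given in section 2.16 at the same time, so that the figure can be checked. The cost is wording only. The sample size already assumes this analysis, and recruitment, treatment and data collection are unchanged.

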### 2.6. Randomization

A total of 88 subjects with KOA who are eligible per protocol will be randomly assigned to group A plant herbal activated carbon smokeless moxibustion group or group B traditional moxibustion group in a 1:1 ratio. After the investigator and the subject sign the informed consent, the investigator will perform a simple rheumatic examination. The investigator will make a diagnosis based on the knee X-ray film brought by the subject or the knee X-ray performed at the site. Only the subject who meet the inclusion/exclusion criteria will be randomized by a random number table. Then investigator will make a baseline assessment and arrange treatment.

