### 2.12. Primary outcome indicators

The primary outcome measure is the change in pain relative to baseline at the Western Ontario and McMaster Universities Osteoarthritis Index (WOMAC) from baseline to week 24. The most painful knee joint for the subject will be recorded at the baseline, which will be the joint we measured throughout the trial. We will also measure WOMAC pain at week 2, 8, 12, and 24.

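### The primary WOMAC pain comparison is fixed as an unadjusted t test on change; adjusting for the baseline score already collected would usually be more precise at no cost

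*Protocol article*

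**What the plan says.** Section 2.12 of the protocol article defines the endpoint: "The primary outcome measure is the change in pain relative to baseline" on the WOMAC, up to week 24. Section 2.17 then names the variable to be analysed: "The primary outcome measure is the effect value of the WOMAC pain score from baseline". The method that it attaches to this variable is a plain two-group t test. It names no baseline covariate, centre term or longitudinal model, and none appears elsewhere in the article.

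Table 1 (section 2.15) schedules the WOMAC before treatment and at weeks 2, 4, 8, 12 and 24. The later pain scores have a planned use: among the secondary outcomes in section 2.17, WOMAC pain "will be compared at all follow-up time points in both groups". Three hospitals recruit (section 2.2). Eligible subjects "will be randomized by a random number table" (section 2.6), and no stratification by centre is stated.

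Section 2.16 sets a non-inferiority margin of 18.49, with α = 0.025 and 80% power. This gives 38 per group, raised to 44 for 15% dropout.

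**The concern.** The article itself names the primary test, so this is a stated choice and not a detail left to a statistical analysis plan.

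A t test on change subtracts the whole baseline value, which means a slope of 1. If the true regression of week-24 pain on baseline is shallower, the subtraction overcorrects. It adds noise, and a chance difference between the arms at baseline passes into the treatment estimate through regression to the mean. ANCOVA estimates the slope from the data and targets the same difference.

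Two features make precision matter here. The margin is only 10% of the reference improvement. The planned size also has no reserve: 44 × 0.85 = 37.4 expected completers per group, against 38 required.

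**Working it through.** **Inputs from section 2.16.** Reference improvement 184.87; margin 18.49; α = 0.025 (taken as one-sided, since sidedness is not stated); power 80%; 38 per group. The article gives no SD and no assumed true difference. The true difference is taken as 0.

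**Step 1: the plan's own figures.** 0.10 × 184.87 = 18.487, so the margin reproduces. The 38 per group cannot be checked forwards without an SD, so it is solved backwards:

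- Normal approximation: SD = 18.49 × √(38/2) / (1.960 + 0.842) ≈ 28.8.
- Noncentral t: SD ≈ 28.4.

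The t-based value of 28.4 is used below as the SD of change.

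**Step 2: variance of the two analyses.** Let s0 and s1 be the baseline and week-24 SDs and r their correlation. Per subject:

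- Change score: s0² + s1² − 2·r·s0·s1
- ANCOVA (large sample): s1²·(1 − r²)
- Difference: (s0 − r·s1)², which is never negative and is zero when s0/s1 = r.

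**Step 3: equal variances (s0 = s1 = s).** The ratio is s²(1 − r²) / [2s²(1 − r)] = (1 + r)/2. Power uses the noncentral t with 38 per group, margin 18.49 and SD 28.4 × √ratio.

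| r | Variance ratio | Extra subjects the t test needs | Power, t test | Power, ANCOVA |
|---|---|---|---|---|
| 0.3 | 0.65 | 54% | 80.0% | 93.5% |
| 0.5 | 0.75 | 33% | 80.0% | 89.9% |
| 0.7 | 0.85 | 18% | 80.0% | 86.0% |
| 0.8 | 0.90 | 11% | 80.0% | 84.0% |

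The third column is 1/ratio − 1. If the SD of change were 50 (an arbitrary larger value), the t test would have 35.6% power. ANCOVA would have 50.5%, 45.1% and 40.7% at r = 0.3, 0.5 and 0.7.

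**Step 4: a narrower baseline (s0 = 0.7·s1, assumed).** Setting s1 = 1:

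- r = 0.3: change 0.49 + 1 − 0.42 = 1.07; ANCOVA 0.91; ratio 0.85; power about 86%.
- r = 0.5: change 0.49 + 1 − 0.70 = 0.79; ANCOVA 0.75; ratio 0.95; power about 82%.
- r = 0.7: change 0.49 + 1 − 0.98 = 0.51; ANCOVA 0.51; ratio 1.00; no gain.

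**Step 5: chance baseline imbalance (equal variances).** The change-score estimate differs from ANCOVA by (1 − r) times the baseline difference between the arms. With s = 28.4/√[2(1 − r)], one standard error of that difference is s × √(2/38).

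- r = 0.3: 0.7 × 5.51 = 3.9 points
- r = 0.5: 0.5 × 6.52 = 3.3 points
- r = 0.7: 0.3 × 8.41 = 2.5 points

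That is 14% to 21% of the margin.

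**Step 6: centre.** If centre explained an assumed 1% to 10% of the variance, adjusting for it would move power from 80% to between 80.4% and 84.0% (normal approximation, SD 28.8).

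**The case against.** The strongest reply is that nothing here is an error. Under randomisation the t test on change is unbiased and keeps its type I error, and its standard error already allows for chance baseline imbalance. It matches the endpoint in section 2.12 and the improvement scale of section 2.16. No planned power is lost; a possible gain is forgone. All of that stands.

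The size of the gain is also open to challenge, and that stands too. The SD is back-solved, r is assumed, and the equal-variance case is favourable to ANCOVA. Section 2.3 requires a baseline pain score of at least 40 on the visual analog scale. This may narrow the spread of baseline WOMAC pain and move the trial towards step 4.

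A reader might infer three stronger points that the article does not support.

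- **That baseline and the other visits are thrown away.** Baseline enters by subtraction, and the other visits are compared as secondary outcomes. With complete data, an unstructured mixed model with a baseline-by-visit term gives essentially the week-24 ANCOVA estimate, so the earlier visits help mainly when week-24 values are missing.
- **That the t test breaks the intent-to-treat principle in section 2.17.** Week 24 is collected by post (section 2.13) and 15% dropout is planned, but no complete-case rule is stated. The t test could follow imputation, and missing-data handling is commonly left to a fuller document.
- **That the design requires a centre term.** No stratification by centre is stated, and the likely gain is small.

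**Conclusion.** The point holds as a matter of efficiency. The article fixes an unadjusted t test on change as the primary analysis although the covariate that would usually sharpen it is already collected. Validity is not in question.

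In large samples, baseline adjustment is never less precise than the change score. In this trial the gain could run from nil (when s0/s1 = r) to a rise in power from 80% to about 94% (equal variances, r = 0.3). Both ends rest on an assumed r, an assumed SD ratio, a true difference of 0, a one-sided α of 0.025, and an SD of change of 28.4 inferred from the stated 38 per group. The direction is secure; the size is illustrative.

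**What to change.** In section 2.17, name as primary estimate the week-24 treatment difference in WOMAC pain from an ANCOVA with baseline WOMAC pain as covariate. Centre may be added as an optional term.

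An equivalent alternative is a mixed model for repeated measures with treatment, visit, treatment-by-visit, baseline, baseline-by-visit and an unstructured covariance. It also uses weeks 2 to 12 for subjects without a week-24 value, on the assumption that data are missing at random.

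Compare the 95% confidence interval of that difference with the 18.49 margin, and keep the t test on change as a sensitivity analysis.

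The cost is a revised paragraph and slightly more analysis work. No new data, visits or subjects are needed.
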